**2. Project summary**

**2.1. Justification of the project**

Uterine fibroids are a benign but common condition among women in reproductive age. It is one of the most common reasons for hysterectomy since it often causes bleeding problems sometimes leading to anemia. Several alternative treatment regimens have been investigated that could replace surgery. The antiprogesteron, mifepristone, is one of the most promising drugs that have been tested. In addition to the inhibiting effect on the growth of uterine fibroids antiprogestins have been proposed to have an antiproliferative effect on breast tissue.

**2.2. Proposed research**

The purpose of the present study is to evaluate the effect of mifepristone on the volume of uterine fibroids. The study will also address the effect of mifepristone on the breast tissue

**2.3. New features**

An evaluation of the effect of mifepristone on uterine fibroids will give information on whether it is possible to treat uterine fibroids pharmacologically instead of using surgery. If that is the case a large number of hysterctomies could be avoided. It would also be of importance to investigate the proposed antiproliferative effect on breast tissue.

**2.4. Techniques and skills**

The study requires experience in ultrasound technique, experience in cytological fine-needle aspiration technique of the breast and evaluation of the biopsies.

**2.5. Problems anticipated**

Timing of the hysterectomy after the treatment period

**3. Description of the project**

**3.1. Rationale and objectives of the study**

**3.1.1. Rationale**

Uterine leiomyomata are common pelvic tumors occurring in up to 20% of women over 30 years of age, and represent one of the most frequent indications for operative procedures in women of reproductive age. (Buttram et al 1981) The growth of the fibroids seems to be dependent of ovarian steroids and receptors for both estrogen and progesterone have been identified in fibroids (Wilson et al 1980, Soules et al 1982).

That progesterone may play a role in leiomyomata growth is further supported by the finding of a higher mitotic count in leiomyomata obtained during the secretory phase than in the proliferative phase of the menstrual cycle. (Kawaguchi et al 1989)

The antiprogesteron mifepristone is a synthetic steroid hormone that binds with high affinity to the progesterone receptor thereby preventing the effect of progesterone. Administration of mifepristone has various effects on reproductive function, depending on the dose and stage of the menstrual cycle. When administered in the follicular phase of the cycle, mifepristone inhibits the process of follicular maturation and blocks ovulation.

Previous studies have shown positive effects after treatment with mifepristone when administered 25-50 mg daily for 3 months. All women became amenorrhoeic during treatment and the size of the fibroids decreased with approximately 50% (Kettel et al 1994). Studies using even higher doses of mifepristone for longer periods than 3 months have not revealed any significant risk of endometrial hyperplasia (Murphy et al 1995).

Ovarian steroids also have an effect on breast tissue. Concern has been raised about hormone replace treatment (HRT) with estrogen and progesterone. Various antiprogestins have been proposed as effective for inhibiting tissue growth in the breast. It would therefore be of importance to evaluate the effect of antiprogestins on the breast tissue.

Apoptosis (programmed cell-death) and cell proliferation seem to be closely linked according to experimental evidence. Many proteins that can induce cell death are also components of the cell cycle (Meikrantz et al 1995, Huang et al 1997). The balance between cell proliferation and cell death determines tumor growth in the endometrium as well as in the breast tissue. Specific markers for proliferation (Ki-67) and apoptosis (proteins from the Bcl-2- family) have been identified.

If a non-surgical method could be found in the treatment of uterine fibroids it might benefit both the society in forms of reduced cost but most of all, the individual woman. From the preliminary data in vitro it seems possible that antiprogestins could prevent growth or even inhibit development of breast cancer.

**3.1.2. Objectives**

The objectives of the present study are

1. To develop a new non-surgical method for treatment of uterine fibroids
2. To study the effect of mifepristone on the size of uterine fibroids
3. To evaluate factors regulating fibroid growth by comparison with untreated fibroids and normal myometrium
4. To study the effect of mifepristone on the amount of blood loss and pelvic pain in patients with fibroids
5. To study the effect of mifepristone on proliferation of breast tissue
6. To study the effect of mifepristone on body composition and cortisol levels

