**3.3. Design and methodology**

**3.3.1. General outline**

This is a pilot study to evaluate the effect of mifepristone on uterine fibroids. The study will include 40 women with uterine fibroids, recruited from the waiting list for hysterectomy. After inclusion women will be randomized to treatment with mifepristone or a placebo (i.e B-vitamin tablets). An ultrasound examination will be performed at start and repeated every 4th week. The total volume of the uterus will be measured as well as each fibroid, and also a Doppler examination of the blood vessels to the fibroids. An biopsy from the fibroid will be obtained at the same time. Endomtrial biopsies will be obtained prior to study start and at surgery for safety reasons and will undergo histological analyses.

Blood will be drawn for analyses of liver function and hemoglobin values as well as estradiol, progesterone, LH, FSH, SHBG, androstendione and DHEAS once a month. A 24 hour urine collection for cortisol levels will be performed and a measurement of body composition with bioelectrical impedance analysis (BIA). This will give information about body cell mass, fat-free mass and total body water. These tests will be repeated after the treatment period.

Women that have not had a mammography during the last 12 months will be offered to have one before the start of the study. A fine-needle-aspiration, from one breast will be performed before, and after the treatment period, for cytological analyses of apoptotic and proliferative factors i.e. Bcl-2, Ki-67 and receptors for estrogen and progesteron. Fine needle aspirations will be performed at the Dept of Cytology, KS in collaboration with [name].

The women will be given Mifegyne 200 mg tablets or B-vitamins and instructed to divide the tablets into 4 parts. One quarter of the vitamin or Mifegyne tablet (50 mg mifepristone), will be taken orally every other day for 3 months. A diary card will be handed out for self registration of bleeding (days and amount), pelvic pain and any side effects.

After the treatment period the woman will undergo surgery as planned. After the uterus has been removed it will be weighed and biopsies from the myomas will be taken for analysis of apoptotic and proliferative factors i.e. Bcl-2, Ki-67 and steroid receptors. Finally the uterus will be examined by a pathologist as part of the usual routine procedure.

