**3.3.2. Criteria for selection of subjects**

A total of 40 women will be recruited among women that are already on the waiting list for hysterectomy.

Inclusion criteria:

- Uterine fibroids requiring treatment
- Good general health
- Willing and able to participate after giving informed consent

Exclusion criteria

- Need for immediate surgery
- Concomitant hormonal treatment (HRT)
- History of malignant disorder of the breast
- Any contraindication for mifepristone

Criteria for retrospective exclusion

Subjects may be excluded from analysis if one of the following applies:

- Any violation of the study protocol
- Lack of essential data

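### Objective 1 and the New features section point to drug treatment instead of surgery, but every woman is scheduled for hysterectomy and no outcome records whether surgery was still wanted, so the design gives only indirect, on-treatment evidence

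*Protocol*

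**What the plan says.** **Aim.** Protocol section 3.1.2 lists as objective 1 "To develop a new non-surgical method for treatment of uterine fibroids". Section 2.3 says that the evaluation "will give information on whether it is possible to treat uterine fibroids pharmacologically instead of using surgery", and adds that many hysterectomies could be avoided if the answer is yes. Section 2.2 is narrower: "The purpose of the present study is to evaluate the effect of mifepristone on the volume of uterine fibroids", with breast tissue as a further topic. Section 3.3.1 opens with "This is a pilot study to evaluate the effect of mifepristone on uterine fibroids".

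**Design.** Section 3.3.2 has the women "recruited among women that are already on the waiting list for hysterectomy". Study treatment "will be taken orally every other day for 3 months" (section 3.3.1). The same section then states: "After the treatment period the woman will undergo surgery as planned". No condition on response is attached.

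**Measurements.** Ultrasound volume is taken at the start and every fourth week, with monthly blood tests including haemoglobin. For symptoms, "A diary card will be handed out for self registration of bleeding (days and amount), pelvic pain and any side effects". The Statistics section covers myoma volume, bleeding pattern, body composition, laboratory values and tissue assays.

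**Exclusions.** Section 3.3.2 also allows a woman to be left out of the analysis afterwards if the protocol was breached in any way or if essential data are lacking.

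**The concern.** There are two linked problems.

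First, objective 1 has no endpoint of its own. Shrinkage and symptom relief during 3 months of treatment bear on the reasons for surgery, but they do not show that an operation was avoided. No outcome captures a changed need or wish for surgery. Observation after treatment with the uterus in place is not planned, so durability is not examined either. An analysis plan cannot repair this later, because it cannot recover an outcome that was never collected.

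Second, the plan does not say how a woman who responds and then cancels or postpones her operation is handled. She departs from the planned course and lacks uterine weight, surgical tissue and the endometrial biopsy taken at surgery. Under the retrospective exclusion rule she could be dropped from the volume comparison as well, although her ultrasound and diary data are complete. Exclusion would then depend on response to treatment, and the comparison would lose the protection of randomisation.

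**Working it through.** The main point turns on the text. The arithmetic only gives scale.

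**1. Does any planned measurement answer objective 1 directly?**

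| Question | What the protocol collects | Evidence |
|---|---|---|
| Do fibroids shrink on treatment? | Ultrasound every fourth week, both arms | Direct |
| Do bleeding, pain and anaemia improve on treatment? | Diary, monthly haemoglobin | Direct |
| Is surgery still wanted at the end of treatment? | Nothing | Indirect only, through the two rows above |
| Was surgery cancelled or postponed? | Nothing | None |
| Does the effect last after treatment stops? | No follow-up planned | None |

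**2. What the sample size covers.** Inputs from the Statistics section: SD 10, difference 10 (both in percentage points of volume change), one-sided 5%, 90% power. Then n per group = 2 × (1.645 + 1.282)² × 10² / 10² = 17.1, so 18. Allowing 10% drop-out, 18 / 0.9 = 20 per group, 40 in total. The plan's figures reproduce. They concern volume change only; nothing is sized on surgery.

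**3. What one question before surgery could yield (assumed rates).** The documents give no rate. Suppose 40% of treated and 5% of control women would no longer choose surgery, a difference of 35 points.
- SE = √(0.40 × 0.60 / 20 + 0.05 × 0.95 / 20) = √(0.012 + 0.002375) = 0.120.
- 95% half-width = 1.96 × 0.120 = 23.5 points.
- With 8/20 against 1/20, the Newcombe interval, which suits small counts better, runs from about 9 to 57 points.
- Across all possible rates the Wald half-width is largest at 50% in both arms: 1.96 × √(2 × 0.25 / 20) = 31 points.

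Such an item is informative for a pilot but imprecise.

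**4. What exclusion of women who cancel could do (same assumed rates, illustration only).** If all of them cancelled and were excluded, 20 − 8 = 12 treated and 20 − 1 = 19 control women would remain, against 18 per group planned as evaluable.
- Power for volume: 10 / (10 × √(1/12 + 1/19)) = 2.71; 2.71 − 1.645 = 1.07; power about 86%. Loss of numbers is not the main issue.
- Bias, extreme case: suppose volume change is normal with SD 10 and exactly the women with the most shrinkage cancel. Mean shrinkage among those left falls by 10 × 0.386 / 0.60 = 6.44 points in the treated arm and by 10 × 0.103 / 0.95 = 1.09 points in the control arm. The difference is understated by 6.44 − 1.09 = 5.35 points, against a target of 10.

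This is the most that those rates could produce under normality. If cancellation were unrelated to shrinkage, the bias from this source would be nil. The real value is unknown.

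**The case against.** The strongest reply is that this is a matter of scope. Section 2.2 gives the purpose as the effect on volume, section 3.3.1 calls the study a pilot, and the sample size rests on volume alone. Section 2.3 promises information, and its sentence on avoided hysterectomies is conditional. Objective 1 speaks of developing a method, which reads as a programme goal. Section 3.7 expects only more knowledge of medical alternatives. Section 2.1 names bleeding and anaemia as drivers of hysterectomy, and bleeding, pain and haemoglobin are all measured in both randomised arms. Operating on every woman also serves a purpose: it supplies tissue for objective 3 and endometrial histology for safety.

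All of that stands. A reader might infer that the trial cannot say anything about objective 1, and the documents do not support this: the volume and symptom results are relevant, though indirect.

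Three other inferences go too far:
- That follow-up between last dose and surgery is zero. No interval is given, and section 2.5 lists the timing of the operation as an anticipated problem.
- That receptor blockade ends with the last dose. Section 3.6 refers to a long half-life, and nothing is said about regrowth.
- That cancelled operations would remove all fibroid tissue. Section 3.3.1 also describes a fibroid biopsy alongside the ultrasound examination.

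The proposed question is imperfectly blinded. Section 3.1.1 reports that all women became amenorrhoeic on mifepristone in earlier work, so many could guess their arm. Analysis of missing specimens may be left to an analysis plan. However, the exclusion rule is fixed in the protocol itself, and so are the objectives.

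**Conclusion.** The point holds in a limited form. The design supports a short-term, on-treatment comparison of volume and symptoms. It does not support a direct conclusion that hysterectomy can be avoided, or any conclusion on durability, because neither is measured. Objective 1 and section 2.3 therefore reach further than the data will. The stated purpose, the effect on volume, is untouched, and the sample size for it reproduces.

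The exclusion rule is a separate and real weakness: it permits women who respond and cancel to be removed from the volume comparison. The harm depends on how many cancel, whether they are those who shrank most, and whether the rule is applied to them. None of this is known from the documents. The 40% and 5% rates, the 12 against 19 women and the 5.35-point shift are assumed illustrations, and none is a forecast.

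**What to change.** 1. **Objective 1 (section 3.1.2) and section 2.3.** Limit both to the short-term, on-treatment effect on fibroid volume and symptoms before hysterectomy. State that avoidance of surgery and durability cannot be concluded from this trial.
2. **One question.** At the last on-treatment visit, before allocation is disclosed, ask each woman whether she would still choose hysterectomy. Report the answers by arm with an interval suited to small counts, as exploratory, and note that amenorrhoea may have revealed the allocation.
3. **Cancelled operations.** Report cancelled or postponed operations by arm, next to the tissue results. State in section 3.3.2 that not having surgery is not a ground for exclusion from the volume and symptom comparisons.

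The cost is small: two reworded passages, one sentence on exclusions, one question at an existing visit and a count by arm. The downside is a more modest stated aim and one additional item that will be imprecise with 20 women per arm. None of the changes affects treatment, the planned operation or the sample size.

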**3.2. Previous** **similar studies**

Results from previous relevant studies have been described above

**3.3. Design and methodology**

**3.3.1. General outline**

This is a pilot study to evaluate the effect of mifepristone on uterine fibroids. The study will include 40 women with uterine fibroids, recruited from the waiting list for hysterectomy. After inclusion women will be randomized to treatment with mifepristone or a placebo (i.e B-vitamin tablets). An ultrasound examination will be performed at start and repeated every 4th week. The total volume of the uterus will be measured as well as each fibroid, and also a Doppler examination of the blood vessels to the fibroids. An biopsy from the fibroid will be obtained at the same time. Endomtrial biopsies will be obtained prior to study start and at surgery for safety reasons and will undergo histological analyses.

Blood will be drawn for analyses of liver function and hemoglobin values as well as estradiol, progesterone, LH, FSH, SHBG, androstendione and DHEAS once a month. A 24 hour urine collection for cortisol levels will be performed and a measurement of body composition with bioelectrical impedance analysis (BIA). This will give information about body cell mass, fat-free mass and total body water. These tests will be repeated after the treatment period.

Women that have not had a mammography during the last 12 months will be offered to have one before the start of the study. A fine-needle-aspiration, from one breast will be performed before, and after the treatment period, for cytological analyses of apoptotic and proliferative factors i.e. Bcl-2, Ki-67 and receptors for estrogen and progesteron. Fine needle aspirations will be performed at the Dept of Cytology, KS in collaboration with [name].

The women will be given Mifegyne 200 mg tablets or B-vitamins and instructed to divide the tablets into 4 parts. One quarter of the vitamin or Mifegyne tablet (50 mg mifepristone), will be taken orally every other day for 3 months. A diary card will be handed out for self registration of bleeding (days and amount), pelvic pain and any side effects.

After the treatment period the woman will undergo surgery as planned. After the uterus has been removed it will be weighed and biopsies from the myomas will be taken for analysis of apoptotic and proliferative factors i.e. Bcl-2, Ki-67 and steroid receptors. Finally the uterus will be examined by a pathologist as part of the usual routine procedure.

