**3.3.3. Subject allocation**

The women who are willing to participate and fulfill the inclusion criteria will be randomized to treatment with Mifegyne or B-vitamin (control group). The treatment will be double blind. Only the nurse instructing patients on how to divide the tablets will be aware of treatment group. The women will obtain once monthly 6 tablets of 200 mg mifepristone or 6 tablets of B-vitamin of which one quarter of a tablet will be taken every other day.

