# Bleeding pattern, BIA and laboratory analysis will be compared using the students-t-test.

For evaluation of immunohistochemistry and molecular biology assays of uterine and breast tissue the paired and unpaired Wilcoxon´s tests will be used as appropriate.

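### Cortisol in objective 6 rests on two 24-hour urine collections with no planned completeness check, which costs precision and is cheap to remedy

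*Protocol*

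**What the plan says.** Protocol section 3.1.2 lists as its sixth objective "To study the effect of mifepristone on body composition and cortisol levels". Section 3.3.1 gives the measurement: "A 24 hour urine collection for cortisol levels will be performed". Bioelectrical impedance is named alongside it, followed by "These tests will be repeated after the treatment period". That makes one urine value at the start and one after treatment.

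No other cortisol measure is planned. The monthly blood samples cover liver function, haemoglobin and "estradiol, progesterone, LH, FSH, SHBG, androstendione and DHEAS once a month"; cortisol is not among them.

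On analysis, the Statistics section says "Bleeding pattern, BIA and laboratory analysis will be compared using the students-t-test". It does not say whether values are raw, log-transformed, indexed or expressed as changes.

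On allocation, section 3.3.3 says "The treatment will be double blind".

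**The concern.** A 24-hour output is proportional to the share of the day's urine that reaches the container. An incomplete collection reads as low cortisol and an over-collection as high.

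The protocol names nothing that would reveal either. It mentions no creatinine, recorded volume, start and stop times, or rule for rejecting or repeating a collection. The patient's own record does not help: "A diary card will be handed out for self registration of bleeding (days and amount), pelvic pain and any side effects". The exclusion ground "Lack of essential data" in section 3.3.2 is generic, and a collection that is incomplete but unnoticed would not trigger it.

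At stake is how a null result can be read. With one value before and one after in about 18 women per arm, a finding of no cortisol effect could reflect no effect or poor collection, and the planned data could not tell these apart. What is assayed in the urine must also be settled when samples are taken. If creatinine and volume are not recorded and no sample is kept, a later analysis plan cannot recover them.

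**Working it through.** **The plan's own figure.** The only calculation in the protocol is for fibroid volume: SD 10%, difference 10%, 90% power, one-sided 5%.

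- n per group = 2 × (1.645 + 1.282)² × (10/10)² = 17.1, rounded up to 18.
- With 10% drop-out, 18 / 0.9 = 20 per group, 40 in total.

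This reproduces exactly and is unaffected by the point. No calculation is given for cortisol.

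**Inputs for cortisol.** From the protocol: 18 evaluable women per arm and two collections per woman. The documents do not give the following, so they are assumed:

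- *b*, the SD of the before-to-after change in log cortisol with complete collections: 0.30, and 0.40 as an alternative.
- *c*, the CV of completeness per collection: 5% to 30%.
- True effect: a 35% rise, ln(1.35) = 0.300.
- Test: two-sided 5%.

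**Formula.** Completeness error is multiplicative, so on the log scale it adds about c² per collection. Two collections enter each change, so SD = √(b² + 2c²). Power comes from the noncentral t distribution with 34 degrees of freedom and noncentrality (0.300 / SD) × √(18/2).

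| c | SD, b = 0.30 | Power | SD, b = 0.40 | Power |
|---|---|---|---|---|
| 0 | 0.30 | 83% | 0.40 | 59% |
| 5% | 0.31 | 81% | 0.41 | 58% |
| 10% | 0.33 | 75% | 0.42 | 54% |
| 20% | 0.41 | 56% | 0.49 | 43% |
| 30% | 0.52 | 39% | 0.58 | 32% |

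**A second framing that needs no assumed effect.** Take whatever effect complete collections would detect with 80% power at 18 per arm, and let *b* run from 0.3 to 0.5. By normal approximation, power becomes 72–77% at c = 10%, 53–68% at c = 20% and 37–57% at c = 30%.

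**Would indexing to creatinine help?** Dividing by creatinine from the same urine cancels completeness error but brings in creatinine's own day-to-day variation, CV *k*. The SD becomes √(b² + 2k²), so indexing gains only when k is below c. With b = 0.30:

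- k = 10%: SD 0.33 and power about 75% whatever c is. This gains at c = 20% or 30%, is neutral at 10%, and loses at 5% (75% against 81% for total cortisol).
- k = 20%: power 56%, no gain at c = 20%.

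All these figures are for change scores. They are not the power of a model with the start value as covariate.

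**The case against.** The strongest case against has four parts.

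*Silence is not exclusion.* Section 3.3.1 is a general outline without assay-level detail, and the protocol sends hormone analyses to Clinical Chemistry without describing procedures. A reader might infer that collection error can be neither detected nor removed, that values will be compared uncorrected, or that women collect at home. The documents support none of these. They do not rule out creatinine, do not say on what scale the t-test is run, and name no collection site. What stands is narrower: no check is planned in the protocol, and it refers to no separate laboratory instruction.

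*A 24-hour urine collection is a recognised measure, and nothing stated is false.* True. The point is that the plan leaves the only cortisol measure without a check that must be arranged at collection.

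*The size is assumed throughout.* This stands. The protocol gives no cortisol SD, expected effect, completeness rate or creatinine variation, so the power figures illustrate and do not estimate.

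*Cortisol per creatinine could do harm as the main comparison.* This also stands. Creatinine output depends partly on muscle mass, and objective 6 studies body composition. If treatment changed lean mass, the ratio would move through its denominator, so noise common to both arms would be exchanged for possible treatment-related bias.

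**Conclusion.** The point holds as a minor weakness in measurement. Two 24-hour collections are the sole basis for the cortisol half of objective 6, and the protocol plans no check of completeness, so collection error adds variance to the cortisol comparison.

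A reader might infer that the comparison is biased. The documents do not support that: allocation is randomised and double blind, so collection errors should be similar in the two arms. Nor do they support saying that the trial falls short of a promised power for cortisol, since none was promised. The study is a self-described pilot sized for fibroid volume.

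The loss may be negligible (83% to 81% at a completeness CV of 5%) or large (83% to 39% at 30%), given an assumed SD of log change of 0.30 and a true rise of 35%. The documents do not show where in that range the trial would lie. The fibroid-volume result and the sample size are not affected. This is a cheap improvement.

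**What to change.** 1. In section 3.3.1 and the laboratory section, add that creatinine is measured and volume recorded in each 24-hour urine already planned. Use both to flag implausible collections, by a rule set in advance and applied blind to arm.
2. In the Statistics section, replace the t-test for this outcome with a comparison of total 24-hour cortisol between arms on the log scale, with the start value as covariate.
3. Report cortisol per creatinine as a sensitivity analysis only, stating that its denominator depends on muscle mass.

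Cost: one routine assay on about 80 samples (40 women × 2 collections) and a few sentences of wording. It needs no extra visit or patient procedure and does not change the sample size. If completeness proves good, there is little or no gain in power, but the check documents it and makes a null cortisol result easier to interpret.

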**3.3.5. Admission procedure**

Eligible patients admitted for hysterectomy will be admitted to the study after they have given their informed consent. Forty subjects will be recruited. The following information will be recorded:

-general and gynecological history

-details of normal cycle (duration of cycle and of menstrual bleeding

-height and weight

-a pelvic examination will be done

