## Statistics

*Sample size calculation*Assuming a standard deviation of 10% in the percentage volume change, 18
 subjects per group will be required to detect a difference of at least 10%
 in the percentage volume change between the treated and the placebo groups
 with 90% power, using a one-sided 5% level test. Allowing for a 10%
 drop outs, 20 subjects per group, or a total of 40, will be recruited into
 the trial.

*Analysis*

 Myoma volume: Repeated measures analysis techniques will be used. For each group, the
 change at each time point will be compared with the baseline value and the
 percentage change with respect to baseline will be estimated. A repeated
 measures model with the baseline volume as a covariate will be used to
 compare the volume at different times between the two groups. Changes will
 be plotted on the absolute scale and will also be expressed as percentage
 change with respect to baseline.

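### Objective 4 concerns blood loss and pelvic pain, but the protocol specifies no structured baseline measure of pain or bleeding amount

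*Protocol*

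**What the plan says.** Protocol section 3.1.2 gives as its fourth objective "To study the effect of mifepristone on the amount of blood loss and pelvic pain in patients with fibroids".

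Section 3.3.1 names the instrument, directly after the instructions for taking the tablets: "A diary card will be handed out for self registration of bleeding (days and amount), pelvic pain and any side effects". It gives no date on which the diary starts and no diary period before treatment.

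Section 3.3.5 lists what is recorded at admission. The relevant items are "general and gynecological history", with no content defined, and "details of normal cycle (duration of cycle and of menstrual bleeding". Neither a bleeding amount nor a pain measure is named. Section 3.3.1 adds an indirect marker of blood loss, taken once a month: "Blood will be drawn for analyses of liver function and hemoglobin values".

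On analysis, the protocol states: "Bleeding pattern, BIA and laboratory analysis will be compared using the students-t-test". It does not say whether the variable is an on-treatment value or a change, gives no baseline term and names no test for pain. For myoma volume, by contrast, the Statistics section does use a baseline: a repeated "measures model with the baseline volume as a covariate will be used to" compare the arms.

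**The concern.** Pain and bleeding amount stand out within the protocol because other measured effects have a pre-treatment value. Ultrasound is done at the start, breast aspiration before and after treatment, and urinary cortisol and body composition are repeated after treatment. The two patient-reported outcomes of objective 4 have no such value on the diary's own items.

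Section 3.3.2 requires fibroids in need of treatment but sets no threshold for pain or bleeding, so some women may enter without pelvic pain. A pain-free diary on treatment then means either that pain resolved or that there was none to begin with, and the data cannot tell these apart. Stable differences between women also stay in the error term, and with about 18 to 20 women per arm a chance imbalance in pain or bleeding amount could be neither seen nor adjusted for.

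This is a matter for the protocol. An analysis plan can choose a covariate, but it cannot supply data that were not collected before the first tablet.

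**Working it through.** **The plan's own figure.** The Statistics section begins: "Assuming a standard deviation of 10% in the percentage volume change, 18" women per group are needed to detect a 10% difference with 90% power at a one-sided 5% level.
- n per group = 2 × (1.645 + 1.282)² × (10/10)² = 17.1, rounded up to 18. Exact non-central t power at 18 is 90.2%.
- 18 / 0.9 = 20 per group, 40 in all.

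Both figures reproduce. They concern fibroid volume; no sample size is given for bleeding or pain.

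**Inputs for pain and bleeding amount.**
- 18 evaluable women per arm (protocol, Statistics).
- Assumptions, because the protocol gives no figures: an effect of 0.8 SD, a two-sided 5% test, and a correlation r of 0.3, 0.5 or 0.7 between baseline and on-treatment score.

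**Chance imbalance.** The difference between two baseline means has SD √(2/18) = 0.333 in units of the between-woman SD. The probability that it exceeds 0.5 SD in either direction is 2 × [1 − Φ(0.5/0.333)] = 2 × [1 − Φ(1.5)] = 0.134, about 13%.

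**Precision.** With the baseline as covariate the residual variance is multiplied by 1 − r². The equivalent unadjusted sample size is 18/(1 − r²). The non-centrality parameter is 0.8 × √(18/2) / √(1 − r²) = 2.4 / √(1 − r²), and power comes from the non-central t distribution with 34 degrees of freedom (33 with the covariate, which changes power by about 0.1 percentage point).

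| r | Variance remaining | Reduction | Equivalent n per arm | Non-centrality | Power |
|---|---|---|---|---|---|
| no baseline | 1.00 | 0% | 18 | 2.40 | 64.5% |
| 0.3 | 0.91 | 9% | 19.8 | 2.52 | about 69% |
| 0.5 | 0.75 | 25% | 24 | 2.77 | about 77% |
| 0.7 | 0.51 | 49% | 35 | 3.36 | about 90% |

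**The case against.** **Validity.** In a randomized, double-blind comparison, on-treatment values can be compared without bias and without a baseline. Women who enter without pain are expected equally in both arms. This stands: the loss is in precision, in protection against chance imbalance and in describing change within women.

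**Silent text.** A reader might infer that the recorded bleeding duration goes unused, or that the comparison rests on values after the start of treatment alone. The protocol supports neither. A t-test on change would use the recorded duration, and the protocol does not say which variable is tested. The diary's start date is not given; its place in the text only suggests the start of treatment. The missing test for pain may also sit in an analysis plan that is not shown.

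**Other sources.** The gynecological history may hold some symptom information, and monthly haemoglobin reflects blood loss indirectly. Both are real, but neither is a baseline on the diary's items and neither is a pain score.

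**Size of the gain.** The correlations and the 0.8 SD effect are assumptions. One recalled menstruation set against a three-month diary may correlate weakly, and at r = 0.3 the gain is only about four points of power. For bleeding, section 3.1.1 reports that all women in earlier studies became amenorrhoeic on treatment. If that recurs, treated women's bleeding will hardly vary with baseline, and a covariate will help little.

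**Weight.** The trial is called a pilot and is sized on fibroid volume. Objective 4 is one of six and carries no power claim, so low power for it contradicts nothing in the protocol. That limits the weight of the point. It does not remove the gap, since the objective is explicit and the missing data cannot be recovered later.

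**Conclusion.** The point holds in this form: no structured pre-treatment measure of pelvic pain or bleeding amount is specified for an objective about both, and the protocol does not say how the bleeding duration recorded at admission enters the analysis.

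It is a cheap improvement in design and no threat to validity. The size depends on a correlation that the protocol does not give. The power gain for an assumed 0.8 SD effect runs from modest at r = 0.3 to large at r = 0.7, and the lower end may be the realistic one for a recalled baseline. The benefit is expected mainly for pain. The 13% chance of a marked baseline gap needs no assumed correlation; it rests on 18 women per arm and a normal approximation.

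**What to change.** At the admission visit, before the first tablet, have each woman complete the diary items (bleeding days, bleeding amount, pelvic pain) once for her most recent menstruation, and add this to the list in section 3.3.5. In the analysis section, replace the t-test for bleeding with a comparison between arms that has this baseline as a covariate, state the same for pelvic pain, and say that the bleeding duration already recorded at admission is used.

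The cost is one form at an existing visit and one covariate per model. There is no extra visit, procedure or delay. The downside is that the baseline is recalled rather than prospective. Recall taken before treatment does not bias the randomized comparison, but it weakens the correlation and so the gain.
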